# The DARE study of relapse prevention in depression: design for a phase 1/2 translational randomised controlled trial involving mindfulness-based cognitive therapy and supported self monitoring

**DOI:** 10.1186/1471-244X-12-3

**Published:** 2012-01-19

**Keywords:** Randomised controlled trial (RCT), Mindfulness-Based Cognitive Therapy (MBCT), Major Depressive Disorder, translational research, health economics

## Abstract

**Abstract:**

**Trial Registration:**

Australian New Zealand Clinical Trials Registry: ACTRN12607000166471

## Background

The 1 year prevalence of major depressive disorder (MDD) in Australia has consistently been measured above 4% [1,2] and it is commonly a recurrent condition. At least 60% of people who have had one major depressive episode will have another, mostly within 2 years of the index episode [3]. Seventy percent of those who have had two episodes will have a third, and 90% of those with three episodes will have a fourth [4]. Effective interventions targeting relapse, particularly in people with a history of three or more episodes of depression, could dramatically reduce the point prevalence of the condition [5]. Mindfulness-based cognitive therapy (MBCT) is a group-based program that integrates aspects of cognitive behaviour therapy (CBT) with components of a Mindfulness-Based Stress Reduction program [MBSR - [6]]). It was developed specifically with the aim of reducing recurrence rates of MDD by increasing patients' ability to recognize and disengage from depression-related ruminative thought patterns through the cultivation of mindfulness. A recent meta-analysis [7] confirmed a highly significant reduction in relapse for MBCT compared to treatment as usual (TAU) for people with three or more episodes of depression, with effects at least equal to maintenance antidepressant medication. MBCT is now included in the United Kingdom's National Institute of Health and Clinical Excellence (NICE) Guidelines for prevention of depressive recurrence for patients who have experienced three or more episodes of depression [8].

The work reviewed by Chiesa et al [7] could be seen as meeting the core requirements of phase 1 translational research in which the safety and efficacy of treatments for selected volunteers are tested in randomised controlled trials (RCTs) [9]. Although mentioned in the NICE guidelines, MBCT has not been similarly recommended in other countries and its implementation within clinical services is typically not routine. There is a need now to move to phase 2 translational research - the application of MBCT within real-world settings with a view to directly informing policy and clinical practice [9,10]. There are a number of important priorities to consider within a phase 2 agenda for MBCT.

### Advancing the translational research agenda related to MBCT

#### Transportability and effectiveness

MBCT trials to date could be argued as being efficacy studies in which the developers of MBCT either provided the therapy [11,12], or provided direct training [13-15] or direct consultation [16] to the therapists. Hence, a priority for phase 2 translational research is to address the transportability of the program [17] - that is, to what extent can MBCT be successfully adapted and applied in settings away from the original developers. In addition to the general question of replication of MBCT findings, it is unclear what level of training is required to become an effective MBCT facilitator. For instance the Centre for Mindfulness Research and Practice in the School of Psychology, Bangor University offers a Masters course with prerequisites including at least 6-12 months with a personal mindfulness practice and completion of an 8-week mindfulness course. Undoubtedly this makes for a comprehensive and thorough training but the cost and demands on therapists is high when considered against typical training requirements for other brief therapeutic models in regular use (e.g., see http://iptinstitute.com/). The demonstration of positive effects achieved by instructors trained in a briefer and more readily generalisable model could be valuable in establishing the case for transportability of the delivery of MBCT.

#### Antidepressant medication

In considering the general application of MBCT more needs to be known about combination treatment with MBCT and antidepressants [18]. Trials of MBCT to date have typically been structured so as to consider MBCT as an *alternative *to maintenance anti-depressant medication (m-ADM) rather than a complement. This stands in some practical tension with clinical guidelines for treatment of people with 3 or more prior episodes, which generally advise m-ADM for up to 3 years [19]. Only one study to date has examined outcomes for MBCT where participants continue their usual treatment, including m-ADM [16]. At baseline, the majority of participants were taking antidepressant medication with the rate of antidepressant use non-significantly higher in the MBCT group (73%) compared TAU (61%). Of interest, the MBCT relapse rate in this trial was one of the lowest recorded compared to other MBCT groups where anti-depressants was disallowed. Over the course of the follow-up period, the rate of antidepressant use decreased in the MBCT group but not in the TAU group, however, regression to the mean may account for this finding as there were no group differences in the rate of antidepressant medication use at any time point. More detailed research examining the combined role of MBCT and antidepressants is required. Difficulties in interpreting the findings from this study could be seen as an argument for stratification according to m-ADM in a pragmatic study.

#### Longer follow up

To date, the follow-up period in RCTs of MBCT has been limited to around 12 months excepting one 18 month follow-up study [15]. One observational study suggests improvements in depression scores following MBCT are maintained over at least 2 years [20] but its role in relapse prevention has not yet been more rigorously examined over this longer time frame. The vulnerability occasioned by having three or more prior episodes persists over many years [21] so MBCT usefully could be studied for potential protective effect over longer time spans. MBCT involves substantial personal commitment for participants including perhaps significant lifestyle changes in the longer term, so for this reason also, information on enduring benefits is very relevant.

#### Health Economics

Kuyken et al [14] examined the cost effectiveness of MBCT compared to m-ADM. Although not conclusive, this work suggested that MBCT was more expensive than m-ADM over the first 12 months with costs then converging and MBCT becoming cheaper over the subsequent 3 months. The authors speculated that the cost-effectiveness of MBCT may increase over time and recommended examining the cost-effectiveness of MBCT over longer follow-up periods. More generally, later phase translational research questions would be served by a health economics study and analysis taking into account local service context, real-world conditions including combined treatment with anti-depressant medication and multiple economic perspectives.

#### Continuing phase 1 agenda

##### Mechanisms of action

Although a number mediation analyses have been published in relation to MBCT, the mechanisms of action remain unclear. Mediation studies often have been small and hence with low power, or limited by being observational in nature [13,20,22-24]. So to consider some possible mediation factors needing further examination:

• Time spent practicing mindfulness meditation correlates with reductions in mood disturbance and relapse but how much practice is required for therapeutic benefit in MBCT remains unsettled [13,20,25].

• Evidence for the role of mindfulness scores in mediating depressive relapse outcomes in MBCT is inconsistent [23,26].

• There has been some support for proposed interrelationships between mindfulness, rumination and depression in an observational study [20] and from a small RCT [24] but the findings await replication in a larger controlled design.

To date the evidence supporting a central mediation role for mindfulness and rumination mediating outcomes in terms of depression and especially depressive relapse is, at best, patchy.

##### Comorbidity

Anxiety disorders are frequently associated with depression and, importantly, are a significant risk factor for the development of depression [27]. Relaxation, although not a primary goal of the mindfulness practices taught in MBCT, is commonly experienced through many of the exercises [28] and learning of relaxation skills may assist participants with anxiety disorders. Moreover, the process of rumination may be similar in anxiety and depression, although the content may differ [29]. A meta-analysis of previous studies suggests that mindfulness-based interventions may have a positive impact on anxiety [30]. However, the mediation role of anxiety in long-term management of depression with MBCT has not yet been examined.

##### Need to prevent and assess for resentful demoralisation

"Resentful demoralisation" is a well-recognised bias that may arise in control group participants whereby the belief that they are not receiving a desirable treatment negatively affects their attitude and behaviour, and as a consequence, the outcome results. Thus, a criticism that that has been leveled at much of the work so far with MBCT is that the promising findings in favour of MBCT may be a reflection of relative deterioration in the TAU group rather than improvement in the MBCT group [31]. As noted by Everitt and Wessely [32], participants entering a trial "are likely to believe that the new therapy is about to solve all their problems. Why else would it be featuring in the trial?" (p. 16). If a participant is then not provided with this promising new therapy, he or she may feel disappointed and have negative expectations of their ongoing involvement. If such negative expectations are present, the seemingly positive results for the experimental treatment may in fact be accounted for by the negative effects in the control. The control condition in this scenario possibly acquires properties of a nocebo [33]. Given that trial participants in MBCT studies are typically highly vulnerable to depression and therefore negative thinking, this effect could be important to consider in study design.

#### Aims of trial

Within the parameters of phase 2 translational research, the aim of this effectiveness study is to examine the clinical impact and health economics of MBCT where efforts are made to assess for and prevent resentful demoralization and under real-world conditions - within a population representative of the intended target audience, that is, people with a history of depression regardless of their antidepressant regimen. For a long-term preventive intervention evidence of a longer duration of effect would be more desirable than the 12-18 month periods so far examined and 2-year follow-up is planned in this study. The portability of MBCT training has not been assessed and this project will investigate outcomes from a novel training program using instructors who may not have a long-standing and deep knowledge of the intervention provided.

The secondary aim of the project is to provide for a detailed examination of the mechanisms by which this form of therapy may prevent depressive relapse, with this examination structured in a way so as also to progress the understanding of the clinical applicability of MBCT as a treatment for relapse prevention in depression. MBCT may act to reduce relapse through a number of mechanisms outlined in the model shown in Figure 1. According to this model, the two primary mediators for outcome in terms of reduced depressive relapse are 1) increased mindfulness and 2) improved relaxation skills which occur as the result of adopting a meditation practice. We have postulated that these factors may have positive downstream effects on other secondary mediating factors such as rumination, neuroticism, medication adherence and anxiety. Although it will not be practicable to explore validation of this causal nexus fully, we will use it to guide our choice of measures through the research plan that follows.

**Figure 1 F1:**
[figure not shown]
**Proposed mechanisms for MBCT**.

## Methods/Design

### Research design

This study is a prospective, multi-site, single (rater)-blind, RCT using a group comparison design between involving the intervention, MBCT, and a comparison condition, Depression Relapse Active Monitoring (DRAM) with follow-up over 2 years. Both interventions are provided in addition to TAU. All participants receive DRAM with half the sample randomised to additionally receive MBCT. Participants continue their usual treatment during the course of their participation in the trial. We avoid any attempts to standardise routine clinical care including medication beyond the recommendations of DRAM. The study is being conducted in compliance with the Helsinki Declaration and has been approved by the following governing ethics committees: Alfred Hospital Ethics Committee (280/07); Barwon Health Research and Ethics Advisory Committee (07/86); Monash University Standing Committee on Ethics in Research Involving Humans (CF07/1275-2007/019MCC; CF08/1031-2008000509); Peninsula Health Human Research & Ethics Committee (2007-53); Southern Health Human Research Ethics Committee (07056B); and The Melbourne Clinic Research Ethics Committee (189). Written informed consent is required for all participants.

### The Interventions

#### MBCT

##### Description

MBCT is a manualised program delivered by an instructor in 8 weekly 2-hour group training sessions involving up to 10 clients; optional 3-monthly 'booster sessions' are also delivered. Sessions incorporate mindfulness practices including meditation and also CBT exercises [28]. Homework for participants includes formal daily meditation practices and exercises for the development of mindful awareness within everyday activity.

##### Therapist training

MBCT instructors are selected from a locally-developed MBCT professional training program headed by GM, who was trained by one of the developers of MBCT (ZS). The training program is, we believe, uniquely geared toward efficiently training experienced mental-health clinicians who do not necessarily have any background or knowledge of meditation to be MBCT instructors. Thus, positive results from this trial favouring MBCT would suggest that it can be effectively provided by instructors who may not have a long-standing and deep knowledge of the intervention and who are trained by someone outside of the original developers of the intervention. This will add further evidence in terms of the important issue of the transportability and generalisability of treatment [7].

The training program involves an initial 8-week course that is a variation of the MBCT therapy group but adapted for the training situation, with some variation to the exercises so as to make them more suitable for experiential participation and learning by therapists rather than patients with depression. Since it is not assumed that trainees already have a meditation practice, following the 8-week course, there is a break for a minimum period of 1 month so that participants can consolidate their personal practice and associated learning. The program then ends with an intensive teacher development retreat over 3 full days which continues to emphasise personal practice as well as concentrated and closely coached practice in leading meditations, discussions and other aspects of the course (total of 44 hours training).

##### Quality control

MBCT sessions are video-taped with the patients' permission (camera visual field focused on clinician) for the purposes of supervision and assessing treatment fidelity. An independent audit of the therapy will be undertaken across the therapy groups using two sessions randomly selected from each group. Sessions will be rated by a clinical psychologist with training and experience in MBCT using the MBCT-Adherence Scale [34].

#### Depression Relapse Active Monitoring (DRAM)

To reduce the discrepancy between groups in treatment expectation and thus mitigate against the risk of triggering resentful demoralisation, we developed a comparison condition called "Depression Relapse Active Monitoring" (DRAM) as an alternative to a TAU-only control. DRAM comprises training on the management of depression through the monthly self-monitoring that forms part of the research assessments. To support DRAM, participants are provided with a manual (also available on the project website) and a wallet-sized card which has self-monitoring items, emergency phone numbers and project contact and web details printed on it. Training in DRAM is provided by research assistants during the intake assessment interview. By being able to fairly present the project as having a potential benefit for all participants, we expect to not only reduce the potential for resentful demoralization but also selection bias. The project title, marketing name and marketing materials have also been developed so as to reflect both conditions in an unbiased manner.

### Power analysis

A power analysis was conducted using estimates of annual relapse rates obtained from the literature. Systematic reviews and meta analyses were mainly utilised including: no treatment (or placebo) only [35-38]; psychological treatment alone; effect in recurrent depression of medication alone [35,37,38]; and combined psychological and pharmacotherapy [39,40]. From these sources, anticipated relapse rates over a 2-year period were: no treatment, 56%; MBCT alone, 31%; medication alone, 31%; and MBCT and medication together, 15%. Based on findings from recruitment in our pilot study, we assumed that 70% of the sample would be taking at least some reasonably effective dose of medication, and 30% would not. Applying the subgroup specific odds ratios suggested the following relapse rates as likely over a 26-month period: MBCT group 21.5%; and DRAM group 41.7%. A power analysis showed that to detect this difference using an uncorrected chi-squared statistic at 80% power and α = 0.05 would require a sample size of 82 participants to complete the full 26 months in each of the MBCT and DRAM groups [41]. Further, assuming a dropout rate of 20% led to a recruitment target of 102 participants for each group.

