##### Time to first clinical intervention

We expect an active property of DRAM in prompting participants to seek help for depressive symptoms at an earlier stage than would occur without this self-monitoring intervention. Thus, although providing some control for treatment expectation and ethically optimising the design, this intervention may reduce the between-group differences with respect to depressive relapse so that time to first clinical intervention is an important adjunctive measure. The General-practice Users' Perceived-need Inventory (GUPI) short form [47] is a three-item measure of perceived need for mental health care that was slightly modified to assess whether there had been a clinical intervention in the past 3 months, and if so, when this was initiated. Study design also includes tracking of medication changes over the course of the project with onset of an antidepressant or increase in dose assumed to signal an incipient relapse.

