The need to balance competing questions of interest is an important consideration in the design of RCTs. For example, the recommended comparator for a health economic analysis is a TAU control [70], while an active alternative treatment is likely to provide the most information for studies investigating mechanisms of action [e.g., [71]]. As an effectiveness trial, a health economic analysis is an important aspect of the present study so favouring the selection of a TAU control in the design. However, we had the additional need to control for the potential bias of resentful demoralization and so the self-monitoring intervention DRAM was introduced as an addition to TAU. This is likely to mean that episodes of depression are picked up and treated earlier than would be the case without such monitoring and possibly lead to a relative weakening of the between-group effects for standard symptom measures [72]. Nevertheless, we predict that the impetus to access treatment prompted by DRAM will, if anything, increase between-group differences in the health economic evaluation and so this will form a critical focus for examination. In addition, with respect to relapse outcomes, substantial reliance will be placed on measures relating to time to clinical intervention.

Historically, health care systems have been heavily oriented to the treatment of illness, rather than to its prevention, resulting in costs that have been described as spiralling out of control [73]. The argument has been put forward that where preventative and especially "low tech" interventions such as mindfulness-based interventions are available, priority should be given to exploring how best to implement them for greatest impact [73]. The results of this trial, including an examination of clinical, functional and health economic outcomes, will be used to assess the role that this treatment approach may have in recommendations for treatment of depression in Australia and elsewhere. We expect that the findings from this research will consolidate the evidence-base to guide the decision to fund MBCT and to seek to promote its availability to those who have experienced at least three episodes of depression.

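### The 26-month design rates come from linear 26/24 scaling rather than the odds-ratio step described, and the DRAM rate contains no DRAM effect, so power is about 77–78% before any benefit of DRAM

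*Protocol article*

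**What the plan says.** The Power analysis section gives anticipated 2-year relapse rates for four treatment situations: "no treatment, 56%; MBCT alone, 31%; medication alone, 31%; and MBCT and medication together, 15"%. On the medication mix it says: "we assumed that 70% of the sample would be taking at least some reasonably effective dose of medication, and 30% would not". It then attributes the 26-month design rates to an odds-ratio step: "Applying the subgroup specific odds ratios suggested the following relapse rates as likely over a 26-month period: MBCT group 21.5%; and DRAM group 41.7"%. The sample size is found "using an uncorrected chi-squared statistic at 80% power and α = 0.05", giving 82 completers per arm.

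Under Research design, every participant receives DRAM on top of usual treatment, and half are randomised to MBCT as well. Under Time to first clinical intervention, the authors expect DRAM to be active in prompting earlier help-seeking and warn that "this intervention may reduce the between-group differences with respect to depressive relapse". The Discussion adds that earlier detection and treatment could "possibly lead to a relative weakening of the between-group effects for standard symptom measures". Neither place gives a size for this effect.

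**The concern.** There are two separate faults in how the design rates are built.

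- **Derivation.** The method named in the text does not produce the published pair of rates. Simple averaging followed by multiplication by 26/24 does. A cumulative risk does not grow in proportion to time, because people who have already relapsed cannot have a first relapse again. Linear scaling therefore overstates both rates and widens the absolute difference on which the chi-squared test depends.
- **Comparator.** The rate given for the DRAM group has no DRAM term in it. The plan thereby sets to zero an effect that it elsewhere names as a possible threat to the primary contrast, and it does not say so in the power paragraph.

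At stake is how far the stated 80% can be relied on when the relapse comparison is interpreted. A reader of the power paragraph alone would not know that the figure depends on a favourable scaling and on DRAM having no effect on relapse.

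**Working it through.** **Inputs (all from Power analysis).** 2-year relapse: no treatment 0.56, MBCT alone 0.31, medication alone 0.31, both 0.15. Medicated 0.7, unmedicated 0.3. Uncorrected chi-squared, α = 0.05 (sidedness not stated; two-sided reproduces the plan's figure), 82 completers per arm.

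**1. The plan's sample size.** With p1 = 0.215, p2 = 0.417 and mean 0.316:

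n = [1.96·√(2·0.316·0.684) + 0.842·√(0.215·0.785 + 0.417·0.583)]² / 0.202² = 81.96, so 82 per arm.

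Power = Φ{[Δ√n − 1.96·√(2p̄q̄)] / √(p1q1 + p2q2)} = 80.0% at n = 82. The arithmetic from the stated rates to 82 is correct.

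**2. Where the rates come from.**

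- Control: 0.7·0.31 + 0.3·0.56 = 0.385; × 26/24 = 0.4171, stated as 41.7%.
- MBCT: 0.7·0.15 + 0.3·0.31 = 0.198; × 26/24 = 0.2145, stated as 21.5%.

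Both arms match. The control figure uses only medication alone and no treatment.

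**3. Other ways to reach 26 months, still with no DRAM effect.** The implied odds ratios are:

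- unmedicated: (0.31/0.69)/(0.56/0.44) = 0.353
- medicated: (0.15/0.85)/(0.31/0.69) = 0.393

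Under a constant hazard within subgroup, the 26-month risk is 1 − (1 − p)^(26/24): 0.56 becomes 0.589, 0.31 becomes 0.331 and 0.15 becomes 0.161.

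| Route | MBCT | Control | Power at 82 | n per arm for 80% |
|---|---|---|---|---|
| As stated (linear) | 21.5% | 41.7% | 80.0% | 82 |
| Constant hazard in each subgroup | 21.2% | 40.8% | 78.0% | 87 |
| Odds ratios on linearly scaled control rates | 22.2% | 41.7% | 77.0% | 89 |
| Odds ratios on constant-hazard control rates | 21.5% | 40.8% | 76.9% | 89 |

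For the second row, control is 0.7·0.331 + 0.3·0.589 = 0.408 and MBCT is 0.7·0.161 + 0.3·0.331 = 0.212. For the third row, the scaled control risks are 0.336 and 0.607, the odds ratios turn these into 0.166 and 0.353, and 0.7·0.166 + 0.3·0.353 = 0.222. No odds-ratio route gives 21.5% and 41.7% together.

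**4. If DRAM lowers relapse.** The size is an assumption: a relative reduction of 10% or 20% in the stated control rate (0.417·0.9 = 0.375; 0.417·0.8 = 0.334), with 82 per arm. The overall odds ratio implied by the stated rates is (0.215/0.785)/(0.417/0.583) = 0.383.

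| What happens in the MBCT arm | Power, 10% cut | Power, 20% cut |
|---|---|---|
| MBCT odds ratio held at 0.383 (18.7%; 16.1%) | 77.0% | 73.1% |
| Same relative cut (19.4%; 17.2%) | 73.7% | 66.6% |
| No benefit from DRAM (21.5% in both) | 61.6% | 39.7% |

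These rows start from the stated rates, so they isolate the DRAM assumption. Started instead from the constant-hazard pair (21.2% versus 40.8%, with control reduced to 0.408·0.9 = 0.368 or 0.408·0.8 = 0.327), the same formula gives about 2 points less in each cell: 75%/71%, 72%/64% and 59%/38%.

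**The case against.** The best defence has four parts.

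- **The sample-size arithmetic is right.** This stands in full. The fault lies in the input rates and in how they are described. A reader might infer that 82 is a miscalculation, but it is not one.
- **The odds-ratio step is not spelled out and has no unique form.** Odds ratios may have been used earlier, to obtain the 2-year rates from the literature. One odds-ratio route, with constant-hazard control rates, even returns the stated 21.5% for MBCT. This stands to the extent that no single odds-ratio answer can be called the correct one. But the sentence attributes the 26-month rates to that step, the published pair matches averaging and linear scaling in both arms, and every alternative tried gives 77–78%.
- **The dilution risk is disclosed and partly handled.** The article names it and adds time to first clinical intervention as an adjunct measure, on which the Discussion says it will lean heavily for relapse outcomes. That is a fair response to interpretation. It does not alter the power stated for the comparison of relapse proportions.
- **The wording on DRAM is hedged, and the planning rates are uncertain anyway.** A reader might infer that the plan firmly expects DRAM to shrink the relapse difference, or that true power is 62% or 40%. The documents support neither. What they expect is earlier help-seeking; the effect on the relapse contrast is put as a possibility, with no size. The 62% and 40% require that DRAM help only those without MBCT, although both arms receive it. The literature control rates carry their own uncertainty, since some are described as no treatment or placebo and the trial also recruits severely affected patients. The net error in the control rate is therefore not established.

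That both arms receive DRAM does not make it cancel out. With a constant relative risk or odds ratio, lower rates in both arms shrink the absolute difference, and power falls.

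**Conclusion.** The point holds in a limited form. The derivation described is not the one used, and the linear scaling is favourable: on the plan's own inputs, 82 completers per arm give about 77–78% power, an overstatement of 2–3 points. This part needs no outside assumption beyond a constant hazard or constant odds ratios over two extra months.

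In addition, the stated power is conditional on DRAM having no effect on relapse, a condition that the paragraph does not state and that the article itself treats as doubtful. Given the plan's other inputs, any DRAM benefit lowers power further. The amount rests wholly on an assumed effect size: 77% to 74% for a 10% reduction and 73% to 67% for a 20% reduction if the MBCT arm shares the benefit, with 62% and 40% as the extreme. The documents do not show that the trial is badly underpowered, and they do not show that a non-significant result would be misread.

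**What to change.** Restate the power paragraph as follows.

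1. Describe the calculation actually used: the 70/30 weighting of the four 2-year rates, then the extension to 26 months.
2. Replace multiplication by 26/24 with a valid scaling, for example a constant hazard within each medication subgroup (21.2% versus 40.8%). If odds ratios are to be kept, give them and show how they were applied.
3. State power at 82 completers per arm as about 77–78% if DRAM has no effect on relapse.
4. Show power for DRAM relative reductions of 0–20%, labelled as an assumption, and say for each line whether the MBCT arm shares the benefit.

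This is a change of text only, with no change to enrolment. The cost is a slightly less favourable stated power.
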